## Abstract

**Background:**

The field of neuroscience has discovered that gamma oscillations (30–100 Hz) in the brain play a key role in neuroplasticity, information conduction and neuroprotective mechanisms. Electroacupuncture stimulation (ES) is a modern treatment method that combines the advantages of Chinese acupuncture with those of electrical stimulation, and is widely used in the field of stroke rehabilitation. At present, there is a lack of research on the clinical efficacy and mechanism of applying gamma frequency (40-Hz) ES, a new neuromodulation mode of integrated Chinese and Western medicine, to induce gamma oscillations and promote the rehabilitation of upper limb motor function in stroke patients.

**Methods and analysis:**

This trial uses a randomized, double-blind and controlled method to evaluate the effect of 40-Hz ES of LI11 (Quchi) acupoint on upper limb motor functional rehabilitation in stroke patients. Based on this new rehabilitation program combining Traditional Chinese medicine with modern technique, all patients will receive baseline assessment, 1-week post-intervention assessment and 2-week post-intervention assessment. The primary outcomes are the Fugl-Meyer Assessment Upper Extremity Scale. The secondary indicators include electroencephalogram, National Institutes of Health Stroke Scale, Mini-mental State Examination and Modified Barthel Index.

**Discussion:**

This trial offers novel perspectives on the application of 40-Hz electroacupuncture stimulation in neural oscillation regulation and the effectiveness of this clinically widespread technique in treating upper extremity dysfunction after a stroke and improving patients’ quality of life. The results of this study will contribute to the scientific community’s understanding of the potential mechanisms of this novel neuromodulation method, including changes in neural network connectivity, and improve existing clinical treatments to benefit more stroke patients.

**Clinical trial registration:**

https://www.chictr.org.cn/showprojEN.html?proj=217786, identifier ChiCTR2400082208.

## Introduction

1

Stroke is the damage of the brain in molecular cells, neural loops and brain network connection caused by the abnormal blood supply caused by the obstruction or rupture of brain blood vessels (1). The total number of prevalent strokes, deaths, and disability-adjusted life years due to stroke increased steadily from 1990 (2). Stroke remains the second-leading cause of death and the third-leading cause of death and disability combined in the world (3). In the context of the demographic development with an aging population, the number of stroke patients is expected to increase significantly in the coming years (4). Motor impairment after stroke typically affects about 80% of patients (5). The incidence of upper limb motor dysfunction in stroke patients is as high as 55 to 75%, and more than one third of persistent upper limb motor dysfunction remained in patients even 6 months after onset (6). This dysfunction is mainly manifested as decreased muscle strength, increased muscle tension and abnormal movement mode, which often causes limb swelling, pain and other discomfort, seriously affects the daily life of patients, and brings great physical and psychological burden to patients and their families (7). Clinical trials have shown that routine rehabilitation intervention is not significant in improving the neurological recovery after stroke, so it is a top priority to seek new stroke rehabilitation therapy (8).

Studies have proved that stimulating the brain is an effective neuromodulation means to promote post-stroke rehabilitation and brain function recovery (9). In recent years, sensory stimulation (such as optical flicker stimulation, sound stimulation, tactile stimulation, etc.) has been proved to be a new non-invasive Neuromodulation technique with clinical application prospects, which has positive significance for improving the rehabilitation status of stroke patients (10–14).

Gamma oscillations (30–100 Hz), a synchronous neural activity common in many brain regions, are thought to be a functional feature of brain networks (15–18). This functional characteristic of the brain will change after stroke (19). Gamma oscillations have been demonstrated to promote neuroplasticity and neuroprotection by regulating synaptic connections and reducing neuronal damage with inflammatory responses in microglia (1, 20). Studies have proved that gamma oscillations enhance synaptic strength and modify neural network connections, promoting neuroplasticity and facilitating the reorganization and repair of damaged neural pathways in the brain, which underpins the recovery of upper limb motor function (21). Additionally, a recent research has demonstrated a significant positive correlation between increased gamma power and the FMA-UE scores of moderate to severe stroke patients during the recovery period (22). Inducing gamma oscillations has shown significant potential in promoting upper limb motor function recovery post-stroke, offering novel strategies and approaches for neurorehabilitation.

Previous trials have proved that a specific frequency of sensory stimulation as a neuromodulation technique, can provide a more comprehensive stimulation, activate sensory receptors induce brain gamma oscillation, activate the damaged nervous system, promote nerve recovery, by increasing the cerebral cortex excitability and arousal, improve the ischemic blood supply stimulation nerve function reconstruction (23–25). Sensory stimulation therapy has a low risk and fewer side effects, and currently there are only reports of using 40-Hz sensory stimulation to stimulate gamma oscillations to promote the recovery of cognitive function in Alzheimer’s disease mouse model or patients (26–29). There is a lack of research on the clinical efficacy and mechanism of applying 40-Hz sensory stimulation to induce gamma oscillations and promote the rehabilitation of upper limb motor function in stroke patients.

Electroacupuncture stimulation (ES), a modern treatment method that combines the advantages of acupuncture in traditional Chinese medicine with the advantages of electrical stimulation (30, 31), is selected as the stimulation method for this trial. ES produces physical stimuli at specific acupuncture points that are detected by sensory receptors, whose activation triggers peripheral sensory neurons to transmit signals to the spinal cord, where the sensory information is processed locally to elicit reflexes and is then transmitted to the brain for nervous regulation (32–34). ES as a form of sensory input, has been shown to correct abnormal brain activity by having the ability to alter the frequency, amplitude, and synchronization patterns of neural oscillations, thereby promoting brain function and aiding in neurological rehabilitation (27, 31). Studies have proved that electroacupuncture stimulation of LI11 can reduce neurological deficits and cerebral infarction volume, inhibit neuronal apoptosis and autophagy, and exert neuroprotective effects (35–37). Previous trials have proved that ES can effectively improve the motor function of the upper limbs in stroke patients (38).

Studies have proved that five major different mechanisms are involved in the beneficial effects of ES on ischemic stroke rehabilitation: Promotion of neurogenesis and cell proliferation in the central nervous system, Regulation of cerebral blood flow in the ischemic area, Anti-apoptosis in the ischemic area, Regulation of neurochemicals, Improvement of impaired long-term potentiation and memory after stroke (39). While traditional electroacupuncture protocols have demonstrated therapeutic efficacy in stroke rehabilitation, they also have limitations and do not fully consider the significance of employing specific frequencies of electrical stimulation. For instance, it remains to be determined whether 40-Hz ES can directly induce gamma oscillations in the brain and thereby harness the unique therapeutic effects of gamma oscillations in neurorehabilitation. The potential of 40-Hz ES on the rehabilitation of upper limb motor function in stroke patients is an area that warrants further investigation. The overall objective of this randomized clinical trial is to seek the clinical efficacy and mechanism of 40-Hz ES to promote upper limb motor functional rehabilitation of stroke patients from the levels of rehabilitation efficacy, neural circuit and brain network.

## Materials and methods

2

### Study design

2.1

The study is a prospective, randomized, double-blind, exploratory, controlled trial design study. In this trial, 50 stroke hospitalized patients who meet the inclusion criteria will be randomly divided into trial group (*n* = 25) and control group (*n* = 25) at a ratio of 1∶1. The patients in the trial group will be given conventional rehabilitation treatment and 40-Hz continuous wave ES on LI11 of the affected upper limb (20 min per intervention, 5 times per week), and the intervention will last 2 weeks as shown in Figure 1. The patients in the control group will be given conventional rehabilitation treatment and sham ES on LI11 of the affected upper limb (20 min per intervention, 5 times per week), and the intervention will last 2 weeks as shown in Figure 1.

**Figure 1 fig1:**
[figure not shown]
Flow chart of the study. FMA-UE, Fugl-Meyer Assessment Upper Extremity Scale; EEG, Electroencephalogram; NIHSS, National Institutes of Health Stroke Scale; MMSE, Mini-mental State Examination; MBI, Modified Barthel Index.

### Sample size

2.2

According to the previous literature, the clinically important difference of the FMA-UE scores ranged from 4.25 to 7.25 points, and the improvement of FMA-UE score of 5.25 marks a significant improvement in upper limb motor function (40). Let *α* = 0.05 (bilateral), the power at 0.80. According software, *n* = 20 can be obtained, and with a drop-out rate of around 20%, the sample size required for each group is 25 cases each. Furthermore, we will establish robust communication protocols during the study to minimize participant dropout and ensure adequate final sample size. Before the study begins, we will thoroughly explain its importance and significance to participants, fostering their comprehension and willingness to cooperate. Throughout the study, we will promptly address any questions or concerns that arise, maintaining participant engagement.

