### Inclusion/exclusion criteria

2.6

The inclusion criteria for the participants are the following:

Meet the criteria for ischemic stroke in the Chinese Guidelines for the Diagnosis and Treatment of Acute Ischemic Stroke 2023, and confirmed by CT or MRI of the head.The patient had a first-time stroke with unilateral hemiplegia.Onset ranged from 2 weeks to 3 months, and vital signs were stable.Age 45–80 years old.The patient had upper limb motor dysfunction in clinical manifestations, and FMA-UE scores in the 0–30 range.The patient can sit independently for 1 h or more.Patients who are in stable condition, conscious, have no aphasia or disorder, can understand the content of the scale, and cooperate with examination and treatment.The patient has not taken any sedative medication or muscle relaxant for 2 weeks.Informed consent to this trial, and signed written informed consent.

The exclusion criteria for the participants are the following:

Patients who are critically ill or in the acute phase and whose condition has not yet stabilized.Patients with deafness, aphasia, or severe cognitive impairment that make it difficult to communicate normally.Patients with systolic blood pressure > 180 mmHg or diastolic blood pressure > 110 mmHg, patients with severe cardiovascular, liver, kidney, blood, digestive, respiratory and other primary diseases, patients with mental illness, malignant tumors, venous thrombosis, osteoporosis, severe bleeding tendency and infection at the treatment site.Patients who are unable to recover with the study protocol or participate in other clinical experiments within 3 months or receive other related treatments in the middle of the study, which may affect the efficacy judgment of this study.Dystonia and previous motor dysfunction caused by other reasons.Pregnant and lactating women.Hemiplegia upper limb with previous trauma and bone and joint diseases.The patient is in a state of severe spasticity, i.e., modified Ashworth scale above grade IIII.The patient has pacemakers, cochlear implants and other instruments and equipment in the body.The patient has had vagus nerve surgery.The patient has sensory disturbances of the skin.

Data integrity is compromised and data will not be included in the analyses when the following:

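### The 80% power claim in section 2.2 rests on an unstated SD, outcome scale and between-arm difference, so n = 20 per group cannot be reproduced and the claim is unsupported

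*Protocol article*

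**What the plan says.** **Section 2.2 (Sample size).** The article reports that "the clinically important difference of the FMA-UE scores ranged from 4.25 to 7.25 points" and that "the improvement of FMA-UE score of 5.25 marks a significant improvement in upper limb motor function". Alpha is set at "0.05 (bilateral), the power at 0.80". Unnamed software then returns 20, which "can be obtained, and with a drop-out rate of around 20%, the sample size required for each group is 25 cases each". No SD, standardised effect, test or formula is given. The section does not say whether final scores or changes were used, or which value in the range was entered as the difference between arms.

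**Section 2.13.1 (FMA-UE).** The 5.25 points reappear as the definition of a clinically meaningful response, which is a threshold for one patient.

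**Sections 2.1 and 2.9.** Both arms receive conventional rehabilitation for two weeks; they differ in real versus sham stimulation. Section 2.1 also labels the trial exploratory.

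**Section 2.6 (Inclusion/exclusion criteria).** Patients enter 2 weeks to 3 months after onset with upper limb dysfunction "and FMA-UE scores in the 0–30 range". The section also lists reasons for leaving a patient's data out of the analysis, including voluntary withdrawal.

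**Section 2.15.1.** A t-test is named for normally distributed data with equal variances, with significance at p < 0.05. No baseline covariate is mentioned, and the choice between final score and change is left open.

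**Section 2.15.2.** An intention-to-treat analysis of all randomised participants is planned.

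**The concern.** Alpha, power and a difference in points do not determine a sample size for comparing means; the SD does the rest. Section 2.2 leaves out the input on which its answer depends most, so a reader can neither confirm nor challenge the 80%.

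The only candidate for the difference raises a second problem. A 5.25-point improvement in a patient is not a 5.25-point difference between arms. If sham-treated patients gain x points on average with rehabilitation alone, treated patients must gain 5.25 + x on average to produce the between-arm difference. The article does not separate the two quantities.

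The stake is how the result will be read. A non-significant comparison in a trial said to have 80% power invites the conclusion that an important effect is unlikely. That conclusion is sound only if the unstated SD was small enough.

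**Working it through.** **Inputs from the article.** Two-sided alpha 0.05, power 0.80, 20 per group before dropout, about 20% dropout, 25 per group randomised; 5.25 points and the range 4.25 to 7.25 (section 2.2); 1:1 allocation (section 2.3); entry FMA-UE 0 to 30 (section 2.6). The SD is not given.

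**Step 1: dropout.** 20 / (1 − 0.20) = 25. This reproduces.

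**Step 2: reproducing n = 20.** For two means, n per arm ≈ 2(z₀.₉₇₅ + z₀.₈₀)² × SD² / Δ². With SD missing this cannot be evaluated, so it was solved backwards.

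- Normal approximation: SD = Δ × √(n/2) / (1.960 + 0.842) = 5.25 × √10 / 2.802 = 5.93.
- Exact noncentral t with 38 degrees of freedom: 80% power needs Δ/SD = 0.909, so SD = 5.25 / 0.909 = 5.77.
- Other ends of the range: 4.25 / 0.909 = 4.67 and 7.25 / 0.909 = 7.97.
- A one-sample or paired calculation for 5.25 points also returns n = 20, at an SD of change of about 7.95. The number 20 therefore does not reveal which test was used.

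**Step 3: power for 5.25 points under assumed SDs.** Two-sample t-test, noncentrality Δ / (SD × √(2/n)). Every SD here is an assumption; 8.66 is 30/√12, the SD if scores were spread evenly over 0 to 30.

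| Assumed SD | 20 per arm | 25 per arm |
|---|---|---|
| 5.8 | 80% | 88% |
| 7 | 64% | 74% |
| 8 | 53% | 62% |
| 8.66 | 46% | 56% |
| 10 | 37% | 44% |

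With 25 per arm, 80% power tolerates an SD up to 6.5.

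**Step 4: power across the article's own range, 20 per arm.** By the same formula:

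| Assumed SD | 4.25 points | 5.25 points | 7.25 points |
|---|---|---|---|
| 5.8 | 62% | 80% | 97% |
| 8 | 37% | 53% | 80% |

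**Step 5: what the choice of analysis does.** Assume SD 8.66 at both baseline and week 2, with correlation ρ between them.

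- t-test on change: SD = 8.66 × √(2(1 − ρ)). This falls to 5.77 when ρ = 1 − (5.77/8.66)²/2 = 0.78.
- ANCOVA on the final score: residual SD = 8.66 × √(1 − ρ²). This falls to 5.77 when ρ = √(1 − (5.77/8.66)²) = 0.75.

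At equal SDs ANCOVA needs the lower correlation, because 1 − ρ² = (1 − ρ)(1 + ρ) never exceeds 2(1 − ρ). The article gives no correlation, so this step shows only that the SD relevant to power depends on a choice the plan leaves open.

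**The case against.** A reader might infer that the 80% is wrong, or that an SD near 5.8 is incompatible with enrolling patients scoring 0 to 30. The article supports neither.

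- An eligibility range does not fix an SD. The 8.66 assumes an even spread; scores clustered in part of the range would give less. It would also be a baseline SD, whereas power depends on the SD of the outcome analysed.
- Section 2.15.1 does not rule out a t-test on change, and the language of improvement in sections 2.2 and 2.13.1 fits one. With SD 8.66 at both visits, a correlation of about 0.78 then gives 80% with no covariate at all.
- The limit of 5.8 depends on 5.25 being the difference. At 7.25 points an SD of about 8.0 suffices.
- Section 2.15.2 plans to analyse everyone randomised. Section 2.6 would drop some withdrawals, so 20 is a fair case, but 25 is the other end and is more favourable.
- A condensed article may leave the SD to the full protocol, and an exploratory trial need not meet a confirmatory standard.

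The first four points stand, and they limit the finding to an unsupported claim. The last stands in part. Leaving out a source could be condensation, but the article itself asserts 80% power and testing at p < 0.05. Its choice of 5.25 and its unadjusted test are also decisions on the page, not omitted detail.

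**Conclusion.** The concern holds in limited form. The 80% power cannot be checked from the article and is unsupported; it has not been shown to be false, and no step in the stated arithmetic is wrong.

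If 5.25 points is the between-arm difference and 20 per arm are compared by a two-sample t-test, the claim needs an SD of at most about 5.8. Over assumed SDs of 7 to 10, power would be 64% down to 37% with 20 per arm, or 74% down to 44% with 25. These ranges rest on assumed SDs, since the article reports no spread of FMA-UE at any visit.

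The confusion of a patient-level improvement with a between-arm difference does not depend on any assumed SD. The exploratory label softens the consequence but does not remove the explicit power statement. The point should be corrected, mainly because a baseline-adjusted analysis would use data the trial already collects.

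**What to change.** Keep 50 patients.

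1. **Section 2.15.1.** Make the primary analysis of FMA-UE at the 2-week assessment an ANCOVA with treatment group and baseline FMA-UE, in place of the unadjusted t-test. Date the change before unblinding.
2. **Section 2.2.** State that 20 completers per arm give 80% power at two-sided alpha 0.05 for a difference of about 0.91 residual SD, which is 5.25 points only if the residual SD is at most about 5.8.
3. **Section 2.2.** Name the SD used and its source. A pooled SD from patients already enrolled, computed without group labels, would serve if no suitable external figure exists. Show power at 4.25, 5.25 and 7.25 points.
4. **Sections 2.2 and 2.13.1.** State the between-arm target and justify it separately from the 5.25-point threshold that defines a responder.

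The cost is wording, one blinded calculation if that route is taken, and an amendment submitted for ethics approval as section 2.19 requires for changed analyses. No extra patients or visits are needed. The downside is that the restated power may be less favourable than 80%.

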### Blinding

2.4

Subjects are blind when receiving the group. All participants were thoroughly informed that the intensity of electrical stimulation administered during the trial might fall below the conventional threshold of human sensory perception. Within the context of the treatment protocol, it is important to note that, although the power indicator of the electroacupuncture apparatus used in the control group was illuminated, the device was carefully configured to ensure that no electrical current was actually delivered to the participants. Investigators who perform ES, clinical assessment, and data analysis will set blind spots for group assignment. Randomization is performed by an independent biostatistician. The biostatistician is the only one who has access to check the file. The allocation list is kept in a separate file on a separate computer under password protection. Since the study code for each participant will not be associated with the group assignment, the person performing the data analysis will not be able to identify the subject’s study group. The current intensity adjustment based on patient tolerance will be executed by an investigator who is distinct from the one responsible for follow - up assessment. The evaluator will remain blinded to the patients’ group assignments. By decoupling the operator from the evaluator, we preclude the evaluator from inferring patient group allocation through procedural information. Moreover, during data recording and analysis, strict anonymity will be preserved for all data, thereby fortifying the blinding technique’s effectiveness.

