### Unblinding

2.5

Staff members who perform the ES and the biostatistician who performs the allocation are not blind. Data will be unblinded when data analysis is completed and statistical tests between study groups need to be performed.

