### Recruitment

2.8

This clinical study will be conducted at the same location with participants without blind spots for treatment task assignment. This study is aimed at patients diagnosed with stroke and associated with upper limb motor dysfunction in the Seventh People’s Hospital of Shanghai University of Traditional Chinese Medicine. Participants will be recruited by distributing pamphlets, websites, and ads on social media. To ensure effective recruitment, research team members will assist in contacting potential participants. Demographic information for each participant will be collected at the first appointment (enrollment). Participants will not be limited by age, gender, or ethnicity. Eligible participants will be informed about the study procedures and any further arrangements are required to be made. Recruitment will be stopped when the number of patients reaches the number of patients expected.

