#### Trial group

2.12.1

All participants were thoroughly informed that the intensity of electrical stimulation administered during the trial might fall below the conventional threshold of human sensory perception and that some may not feel the electrical stimulation. 40-Hz ES will be given at the affected side LI11 (quchi) of the patient, with an intensity starting at 0 mA and adding 0.1 mA each time to avoid pain to the patient tolerance (When the patient develops pain, immediately stop continuing to increase the current and drop 0.1 mA).

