#### Control group

2.12.2

All participants were thoroughly informed that the intensity of electrical stimulation administered during the trial might fall below the conventional threshold of human sensory perception and that some may not feel the electrical stimulation. Sham ES will be given at the affected side LI11 (quchi) of the patient, although the power indicator of the electroacupuncture apparatus used in the control group was illuminated, the device was carefully configured to ensure that no electrical current was actually delivered to the participants.

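### The trial is called double-blind, but the protocol contradicts itself on whether the ES operators are blind, and its participant masking does not fit an active current raised to tolerance against a no-current sham

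*Protocol article*

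**What the plan says.** The abstract and section 2.1 (Study design) give the headline label: "The study is a prospective, randomized, double-blind, exploratory, controlled trial design study".

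**Operators.** Section 2.4 (Blinding) states: "Investigators who perform ES, clinical assessment, and data analysis will set blind spots for group assignment". It adds, of the allocation list: "The biostatistician is the only one who has access to check the file". Section 2.5 (Unblinding) states: "Staff members who perform the ES and the biostatistician who performs the allocation are not blind".

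**Participants.** Section 2.4 says participants are blind. The means described in sections 2.4, 2.12.1 and 2.12.2 are a statement to all participants that the current may be too weak to perceive, and a lit indicator on the control device.

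**Active arm.** Section 2.12.1 delivers current "with an intensity starting at 0 mA and adding 0.1 mA each time to avoid pain to the patient tolerance". If pain occurs, the increase stops and the current is lowered by one 0.1 mA step. Section 2.12.3 repeats this.

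**Control arm.** Section 2.12.2 states: "the device was carefully configured to ensure that no electrical current was actually delivered to the participants".

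**Population.** Section 2.6 lists among its exclusions: "The patient has sensory disturbances of the skin".

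**Evaluator.** Section 2.4 also says that the person who adjusts the current is not the person who does the follow-up assessment, and that the evaluator stays blinded.

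**The concern.** Two things are wrong as written. First, the document gives two incompatible answers on whether the people delivering the intervention know the allocation. Second, the device it relies on to mask participants assumes stimulation that may go unnoticed, whereas the active procedure is steered by what the patient feels.

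The primary outcome, FMA-UE, scores how far the patient completes prescribed movements, 0 to 2 per item (section 2.13.1). Much of it therefore depends on what the patient does in the test, and effort and expectation can enter even when the rater is blind. Participants who believe they know their arm may also engage differently with the broad conventional rehabilitation package in section 2.9, or tell the evaluator what they felt. The assessments fall at the fifth and tenth sessions, when the experience is fresh. A positive result reported as double-blind would claim more protection against these effects than the procedures provide.

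**Working it through.** No figure in the protocol bears on this point, so the check sets the passages side by side.

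**Step 1: can sections 2.4 and 2.5 both be true of the operators?** The phrase about blind spots in section 2.4 is awkward. In a section on blinding, in a list with assessors and analysts, its only sensible meaning is that these people are blinded. Section 2.5 says ES staff are not. Both cannot hold.

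**Step 2: which one fits the procedures?**
- In the active arm the operator raises the current from 0 mA in 0.1 mA steps until the patient's tolerance is reached, and steps back on pain.
- In the control arm the device is configured to give no current, so no patient can report current-related tolerance or pain at any setting.
- An operator running the titration would learn the arm from the patient's response, even without access to the allocation list.
- Section 2.4 itself keeps operator and evaluator apart so that procedural information cannot reveal the group. That precaution presumes the operator holds such information.

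Section 2.5 is therefore the consistent statement, and the operators cannot be blind.

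**Step 3: does the participant masking fit the intervention?**

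| Element | Active arm | Control arm |
|---|---|---|
| What participants are told | Current may be too weak to feel | Same |
| Current delivered | Raised to tolerance; on pain, lowered by 0.1 mA | None |
| How the setting is fixed | By the patient's own sensation | No setting depends on sensation |
| Expected sensation from current | Very likely felt | None |
| Sessions | 5 per week × 2 weeks = 10 | 5 per week × 2 weeks = 10 |

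A setting found by asking for tolerance or pain, then left there or one step lower, is not one that would ordinarily go unnoticed. Excluding patients with skin sensory disturbance makes an unfelt current less likely still. The information given to participants and the active procedure are therefore at odds.

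**Step 4: what follows for each arm?**
- Active: participants told they may feel nothing, who then feel a current titrated to tolerance at up to ten sessions, have strong grounds to infer active treatment.
- Control: participants feel no current, but they were told this can happen, the device is lit, and sham ES is given at the same point. Feeling nothing is compatible with either arm as it was explained to them.

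Doubt about masking is thus clearest in the active arm and is an inference in the control arm.

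**Step 5: what does the blinded evaluator protect?** Keeping operator and evaluator apart guards against a rater who knows the arm from the procedure. It does not change what the patient expects, how hard the patient tries, or what the patient says at the assessment.

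**The case against.** The strongest reply is that the operator conflict is a slip of wording. The rest of section 2.4 treats the operator as informed and shields the evaluator, which agrees with section 2.5. Sole access to the list is not a further contradiction, since allocation travels by envelope (section 2.3). This is fair on intent, and the list-access sentence is not relied on here. But the sentence still places operators among the blinded and has to be corrected.

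The evaluator is blinded and separate, sections 2.3 and 2.4 also provide for blinded analysis, and section 2.12.6 has staff remind participants not to start additional rehabilitation. These safeguards stand and are credited. They reduce rating bias and some co-intervention, but do not restore participant masking.

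Some stronger readings are tempting but not supported:
- **Complete unmasking of participants.** If the titration works as described, up to 25 of 25 active participants and 0 of 25 controls would feel current. That counts sensation, not correct guesses. Controls have a plausible explanation for feeling nothing, and no participant experiences both arms.
- **A known bias on FMA-UE.** The protocol gives nothing from which to size an expectation effect, so none can be set against the 5.25-point difference it names.
- **An open trial by its own admission.** Section 2.8 speaks of "participants without blind spots for treatment task assignment". The sentence is too garbled to count as evidence that participants are unblinded, though it should be reworded.
- **A missing check of masking as an error.** A journal article may leave this to the full protocol. Recording guesses is proposed below as a remedy, and its absence from the article is not held against the plan.

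**Conclusion.** The point holds. The protocol contradicts itself on operator blinding, and the operators cannot be blind under the procedures described. Participant masking is doubtful, most clearly in the active arm, because the information given to participants does not fit a current titrated to tolerance or pain against a sham with no current. Blinded evaluation and analysis, as stated in sections 2.3 and 2.4, can still be claimed; an unqualified double-blind label cannot.

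The size is not known: the protocol gives neither a rate of unmasking nor a magnitude of bias. The conclusion rests on two assumptions: that the titration is carried out as sections 2.12.1 and 2.12.3 describe, and that patients without skin sensory disturbance will ordinarily feel a current raised to tolerance. The trial is declared exploratory, which lowers the stakes of a single result, but the label governs how its primary outcome will be read.

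**What to change.** 1. Reconcile sections 2.4 and 2.5 by removing ES operators from the list of blinded staff, and reword the blinding phrase in section 2.8.
2. Describe the trial as evaluator- and analyst-blinded, with participant masking attempted and operators unblinded.
3. Reconcile the statement that the current may be imperceptible with the titration in sections 2.12.1 and 2.12.3. Which of the two changes is for the investigators; no current setting is proposed here.
4. Use the same stepwise knob-turning and the same questions to the patient in the sham arm, with output off.
5. At the final week-2 assessment, after outcomes have been scored, ask each participant and the evaluator to guess the allocation, and report the guesses by arm. Asking only then avoids prompting participants to work out their arm during treatment.
6. State in advance that, if masking fails, the result is read as a comparison with blinded assessment only.

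**Cost.** Items 1, 2 and 6 are wording, item 3 is wording or procedure, item 4 is a short script, and item 5 is one question per person. The double-blind label is given up. Recruitment began in October 2024 (Trial status), so the procedural changes need an ethics amendment and apply only to later participants. Earlier and later participants will then differ in sham procedure and in whether guesses are available, and the report should say so.
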